### Participant eligibility

PFPS patients were recruited for sports-specialized college students at a university in Beijing. Diagnostic criteria [34–36] are as follows: (1) retropatellar or peripatellar pain for ≥ 4 weeks; (2) at least two induced pains when completing functional activities such as hopping on one foot, going up and down stairs, squatting, running, kneeling, and bending knees for a long time; (3) VAS score ≥ 2 when the pain was the most severe in the last week; (4) Lysholm score < 70; (5) at least two of the following signs were positive: tenderness on the patella or patella circumference, crepitus on the patellofemoral joint surface, Fear test, patellofemoral grinding test, knee extension resistance test, single foot squat test. Inclusion criteria were (1) aged 18–30 years; (2) met the diagnostic criteria and had unilateral involvement; (3) did not receive medication or physical therapy; (4) voluntarily signed informed consent. The exclusion criteria were: (1) damage to the tissues around the knee; (2) structural damage to the knee, such as fracture, meniscus tear, or osteoarthritis; (3) allergy to KT; (4) physical activity Medical contraindications (such as cardiovascular disease); and (5) Inability to adhere to the intervention due to personal or other reasons. All subjects voluntarily signed a written informed consent form before the intervention and were given an explanation of the research process by the researchers, strictly following the ethical standards of the Declaration of Helsinki.

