## Outcome assessment test indicators

### Primary outcome

Visual analog scale/score (VAS): VAS was used to evaluate the pain of PFPS patients before and after intervention [43]. On a 10 cm long walking scale, one side has 10 scales, and the two ends are 0 and 10, indicating no pain and the most severe pain, respectively; the other is colored from light to dark, showing different degrees of pain. When using it, turn the scaled side away from the patient, and let the patient mark the corresponding color on the ruler that can represent their pain level, and score [44] according to the position marked by the patient.Knee joint Lysholm function score (Lysholm): Knee joint function is evaluated by the Knee Joint Lysholm Function Score (LKSS), which has been proven to have good reliability and validity [45]. The parameters of the scale (total score 100) mainly include lameness (5 points), twisting (15 points), pain (25 points), support (5 points), instability (25 points), swelling (10 points), Going up and down stairs (10 points), squatting and standing up (5 points), basically covering all symptoms of patients with patellofemoral joint disease. The size of the score is positively correlated with the functional status of the knee joint of patients, and the higher the score, the better the joint function [46].Static balance: The static balance ability of the dominant side of the subjects was assessed by the UniPedal Stance Test (UST) with eyes closed. UST has been shown to have high scoring reliability (ICC = 0.998) [47], and its test refers to the method of previous literature [48]. Before the formal test, the subject’s heart rate should reach a quiet level, and perform 4 test exercises. At the beginning of the formal test, stand on one foot with eyes closed according to the test requirements, and stop timing when the supporting leg is displaced, eyes are opened, or the non-supporting leg touches the ground. Each subject repeated the test 3 times with 20 s rest intervals, and the average of the 3 test scores was the final test score of the subjects.Dynamic balance: The Star Excursion Balance Test (SEBT) was used to evaluate the dynamic balance ability of the dominant side of the subjects. SEBT is a comprehensive quality, including strength, flexibility, and coordination quality, which is widely used to evaluate the dynamic stability of lower limbs [49], and its test method refers to previous studies [50]. Before the formal test, to reduce the test error caused by the learning effect, the subjects performed the test practice 4 times. In the formal test, the subject (left or right foot) is required to stand on one foot, with both hands on the hip, and the non-supporting leg is extended as far as possible in front of the supporting leg, the back-inward direction, and the back-outward direction, respectively, and the non-supporting leg is retracted and close to the supporting leg, then start the next reach. The subject’s supporting leg moved, the non-supporting leg touched the ground, or the non-supporting leg reached quickly and far rather than sustained force during the test was considered a failure. The subject’s measurement in each direction is 3 times, with a 20-s rest between each time. The average of the 3 test data is the subject’s final score in that direction, and the total comprehensive value is the average of the 3 directions. SEBT has been shown to have good internal reliability (ICC = 0.86–0.94)52 [51] and test–retest reliability (ICC = 0.89–0.93) [52].

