
### Secondary outcome

#### Knee joint isokinetic muscle strength test

The Isomed 2000 isokinetic muscle strength test system in Germany was used to test the isokinetic muscle strength of the dominant side of the subject. After the subjects are fully warmed up, the tester conducts a guided test and conducts adaptive exercises on the test system. In the formal test, a sitting position was used, the thigh and trunk were fixed, the knee joint range of motion was set to be 0–100°, and the test angular velocity was 60°/s. Studies have shown that this angular velocity can better reflect the level of knee flexor and extensor muscle strength [53]. Knee flexion and extension tests were performed 5 times each. The flexor muscles were measured first, and then the extensor muscles were measured. The dominant leg was tested first and then the non-dominant leg was tested. The interval between each test was 60 s, and the average was taken as the final test score. The test index is Relative Peak Torque (RPT), representing the peak torque per unit body weight. The larger the RPT value, the greater the knee joint muscle strength.

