#### Knee joint proprioception test

The German Isomed 2000 isokinetic muscle strength test system was used to test the subject’s dominant knee joint position perception (Knee joint Position PercePtion, KJPP) evaluation. The knee joint position awareness test adopts the passive position awareness reduction method, and the target angle is 45° [54] of knee joint flexion. During the formal test, the subject’s knee joint was driven by the instrument to the target angle, and then the subject felt the angle for 5 s and returned to the starting position. Then, the knee joint was driven by the instrument at a speed of 1°/s. When the subject felt that the target angle was reached, the brake switch was quickly pressed to record the actual angle of the subject. The subject’s position sense is the absolute value of the difference between the actual angle of its reset and the target angle. The smaller the value, the better the position sense.

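### UST, SEBT and KJPP are scored on the dominant leg although patients have PFPS in one knee only and nothing ties dominance to the affected knee; the strength section contradicts itself on the leg scored

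*Protocol article*

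**What the plan says.** Under Participant eligibility, a patient must have "met the diagnostic criteria and had unilateral involvement", so each patient enters with one affected knee. Neither that section, nor the randomization section, nor any outcome section says whether that knee is on the dominant side.

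The leg to be tested is then set by dominance:

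- Static balance (Primary outcome): "The static balance ability of the dominant side of the subjects was assessed by the UniPedal Stance Test (UST) with eyes closed".
- Dynamic balance (Primary outcome): SEBT "was used to evaluate the dynamic balance ability of the dominant side of the subjects". The procedure that follows describes the subject with the words "left or right foot) is required to stand on one foot".
- Position sense (Knee joint proprioception test): the measure is the "dominant knee joint position perception".
- Strength (Knee joint isokinetic muscle strength test): the device is "used to test the isokinetic muscle strength of the dominant side of the subject". The same paragraph later says "The dominant leg was tested first and then the non-dominant leg was tested", and then "The interval between each test was 60 s, and the average was taken as the final test score".

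VAS and Lysholm, the other two measures listed as primary, are not tied to a side.

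**The concern.** The trial's title question is posture control in patients with PFPS. The Discussion names static balance, dynamic balance, knee strength and proprioception as the measures of it, and it attributes the loss of stability to knee pain and lost function. By the protocol's own reasoning, the deficit belongs to the painful knee. A rule that picks the leg by dominance will pick the other leg in some patients.

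Two things are at stake. First, if the healthy leg has less to gain, the effect on UST, SEBT and KJPP is attenuated. A null result could then not be told apart from measurement on the wrong leg. Within one patient, the pain and function scores could also describe one knee and the balance scores the other. Second, for strength, two analysts could compute different relative peak torque (RPT) values from the same recordings and both claim to follow the text.

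**Working it through.** **Step 1. Which leg is measured when the non-dominant knee is the affected one?**

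| Measure | Leg stated | Affected knee measured? |
|---|---|---|
| VAS, Lysholm (primary) | not tied to a side | not in question |
| UST (primary) | dominant | no |
| SEBT (primary) | dominant | no |
| KJPP (secondary) | dominant | no |
| RPT (secondary) | dominant, then both legs | tested under the second statement; scoring unclear |

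For RPT, the average could be over the five repetitions on one leg or over both legs. If it is over legs, every patient's score mixes an affected and an unaffected knee.

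**Step 2. Reproduce the protocol's sample size.** Inputs from Sample size calculation: 4 groups, 3 times, f = 0.25, α = 0.05, power 0.8, giving 64. The section states neither the correlation between visits (ρ) nor the term tested. With m = 3 visits and noncentral F:

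- Between-groups test: λ = f²·N·m / (1 + (m − 1)ρ), df 3 and N − 4. At ρ = 0 and N = 64, λ = 0.0625 × 64 × 3 = 12 and power is 0.813.
- Group-by-time test: λ = f²·N·m / (1 − ρ), df 6 and 2(N − 4). At ρ = 0.2 and N = 64, λ = 12 / 0.8 = 15 and power is 0.820.

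Both settings give 64. At ρ = 0.5 the same formulas give 124 (between groups) and 40 (group by time), so the reproduction depends on an unstated ρ. For dropout, 64 × 1.1 = 70.4 (71 rounded up) and 64 / 0.9 = 71.1 (72 rounded up). Both are consistent with the final 72.

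**Step 3. Attenuation.** Let p be the share of patients whose affected knee is on the dominant side. Let h be the treatment effect on the healthy leg relative to that on the affected leg. With an unchanged standard deviation:

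share of effect kept = p + (1 − p)h, so observed f = 0.25 × [p + (1 − p)h].

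The documents give neither p nor h. Reading f = 0.25 as the effect in the affected leg is a further assumption, because the protocol ties it to no outcome or limb.

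**Step 4. Illustration at p = 0.5.** Then 72 × 0.5 = 36 patients would be tested on the healthy leg. Ranges cover the two settings of Step 2.

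| h | Share kept | f | Power at N = 64 | N for 80% power |
|---|---|---|---|---|
| 1 | 1.000 | 0.250 | 0.81–0.82 | 64 |
| 0.75 | 0.875 | 0.219 | 0.69 | 80 |
| 0.5 | 0.750 | 0.188 | 0.53–0.54 | 108 |
| 0 | 0.500 | 0.125 | 0.24–0.26 | 236–240 |

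**Step 5. Range over p from 0.3 to 0.7.** The number tested on the healthy leg, 72(1 − p), runs from about 50 down to about 22. Power at N = 64 is 0.63–0.75 for h = 0.75, 0.40–0.66 for h = 0.5 and 0.11–0.48 for h = 0. At h = 1 nothing is lost whatever p is.

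**The case against.** Several stronger readings are tempting, and the documents do not support them.

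- *All four postural-control measures miss the affected knee.* Not so for strength. The section also has the non-dominant leg tested, so under that statement the affected knee is always measured. The fault there is an unclear scoring rule.
- *SEBT contradicts itself on the leg.* It does not. A dominant foot may be the left or the right one, so the procedural wording is compatible with the dominant-side rule.
- *The effect will be halved.* That needs p = 0.5 and h = 0. Taping goes on the quadriceps of both legs (Placebo kinesio taping) and the Tan Tui sequence has matching right and left movements. A healthy leg that does not respond at all is therefore unlikely.
- *Chance imbalance in affected side distorts the group comparison.* Allocation is random, and the Statistical analysis section includes a group-by-time term from baseline. Stable differences between limbs largely cancel there. Only a difference in response remains, which means attenuation or imprecision and not systematic bias.
- *The primary outcomes as a whole are compromised.* VAS and Lysholm, and with them the efficacy half of the stated purpose, are untouched.

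There is also a real argument for the dominant leg: it standardises dominance across patients, whereas testing the affected leg mixes dominant and non-dominant limbs. That stands as a small cost, and a covariate can handle it. What no argument removes is that three measures are assigned to a leg without regard to where the disease is. Treating both legs does not turn a healthy leg into a measure of recovery from PFPS.

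**Conclusion.** The mismatch is certain on the text. UST, SEBT and KJPP are assigned to the dominant side, eligibility requires one affected knee, and nothing links the two. In each patient with a painful non-dominant knee, two primary measures and one secondary measure describe the leg without PFPS. It is equally certain that the strength section does not settle which leg, or which average, is scored.

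The consequence for power is conditional. It runs from none (h = 1, or every affected knee dominant) to substantial, and the documents cannot place the trial within that range. The figures above rest on assumed p and h, on a correlation that the protocol does not state, and on f = 0.25 describing the affected leg. They do show that there is little margin. Under the settings that reproduce 64, power starts at 0.81–0.82, and at p = 0.5 a healthy-leg response of three-quarters already takes it to 0.69.

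**What to change.** - Define the affected (index) knee as the analysed limb for UST, SEBT, RPT and KJPP, and use the same limb at all three visits.
- Record the affected side and the dominant side for each patient, and adjust for whether the index limb is the dominant one.
- Report the other limb descriptively where it is tested.
- In the strength section, reconcile the dominant-side statement with the two-leg procedure, and say what the average is taken over.

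The cost is about one sentence per test and a field or two on the case report form. Tests and equipment are unchanged. Strength is already described on both legs; testing the second leg for balance and position sense would add assessment time and is optional. The analysed limbs will mix dominant and non-dominant legs, which the covariate addresses.

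Timing matters. Trial status says the experiments had not started, but the article appeared in August 2023, after the planned start of testing in late November 2022. If testing has already been done on the dominant leg only, the affected leg cannot be recovered by analysis. In that case, record the affected side, report UST, SEBT and KJPP by whether the tested leg was the affected one, and limit the postural-control conclusion accordingly.

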
### Secondary outcome

#### Knee joint isokinetic muscle strength test

The Isomed 2000 isokinetic muscle strength test system in Germany was used to test the isokinetic muscle strength of the dominant side of the subject. After the subjects are fully warmed up, the tester conducts a guided test and conducts adaptive exercises on the test system. In the formal test, a sitting position was used, the thigh and trunk were fixed, the knee joint range of motion was set to be 0–100°, and the test angular velocity was 60°/s. Studies have shown that this angular velocity can better reflect the level of knee flexor and extensor muscle strength [53]. Knee flexion and extension tests were performed 5 times each. The flexor muscles were measured first, and then the extensor muscles were measured. The dominant leg was tested first and then the non-dominant leg was tested. The interval between each test was 60 s, and the average was taken as the final test score. The test index is Relative Peak Torque (RPT), representing the peak torque per unit body weight. The larger the RPT value, the greater the knee joint muscle strength.

#### Knee joint proprioception test

The German Isomed 2000 isokinetic muscle strength test system was used to test the subject’s dominant knee joint position perception (Knee joint Position PercePtion, KJPP) evaluation. The knee joint position awareness test adopts the passive position awareness reduction method, and the target angle is 45° [54] of knee joint flexion. During the formal test, the subject’s knee joint was driven by the instrument to the target angle, and then the subject felt the angle for 5 s and returned to the starting position. Then, the knee joint was driven by the instrument at a speed of 1°/s. When the subject felt that the target angle was reached, the brake switch was quickly pressed to record the actual angle of the subject. The subject’s position sense is the absolute value of the difference between the actual angle of its reset and the target angle. The smaller the value, the better the position sense.

### Safety measurements

Any unexpected adverse events that occurred during the 6-week intervention period will be reported to the research assistant, and the causal relationship between y and Tan Tui exercises and kinesio taping effects will be evaluated. If a severe sports injury or other adverse event occurs, the research assistant will immediately report to the project leader and the Sports Science Ethics Committee of Beijing Sport University; they will decide whether the participant needs to withdraw from the study.

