### Sample size calculation

The sample size was estimated by the software G*Power 3.1.9 [33]. According to the experimental design of 4 (group) * 3 (time) in this study, repeated measures analysis of variance was used to test the research hypothesis. Under the effect size of 0.25, α of 0.05, and power of 0.8, the sample size requirement was 64 people. After considering the dropout rate of 10%, the overall sample size was calculated to be 71 people. At the same time, combined with the proportionality of the sample size between groups, the final sample size was determined to be 72 people, and each group was about 18 people.

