### Data collection

Subject demographics will be collected during the recruitment process. Data on primary and secondary outcomes will be collected by professional outcome assessors at baseline, at 4 weeks of intervention, and at 6 weeks of intervention. All outcome assessors had standardized training on test methods prior to intervention to ensure that all subjects had the same test conditions. To ensure the attendance of students and provide more complete data results, we will provide all students with free professional TT teaching services, free knee pain treatment, and a reward of 100 yuan. It will be released via WeChat after 6 weeks of intervention.

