### Data management

The primary and secondary results of the test will be recorded through the case report form (p-CRF), and the paper version of the data will be processed electronically through the free data management software EpiData Manager on time. Two result evaluators separately reviewed and confirmed the data, and converted it into a format that can be used for statistical analysis.

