## Monitoring

Tan Tui is an aerobic exercise with low risk. This study is not expected to cause any potential harm. Therefore, there will be no data monitoring committee, interim analysis, or stopping rules. We do not anticipate any potential harm. Therefore, there will be no Data Monitoring Committee, interim analyses, or containing rules.

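### The safety rule makes *unexpected* the test for reporting an adverse event, so mild foreseeable events could go unrecorded

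*Protocol article*

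**What the plan says.** The Safety measurements section has two sentences that matter here.

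- The first sets the routine rule: "Any unexpected adverse events that occurred during the 6-week intervention period will be reported to the research assistant". It continues by saying that a causal link with Tan Tui and taping will be assessed, so causality assessment covers the same set of events.
- The second sets the escalation rule: "If a severe sports injury or other adverse event occurs, the research assistant will immediately report to the project leader" and to the ethics committee, which together decide on withdrawal. It does not use the word *unexpected*.

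The Monitoring section says "This study is not expected to cause any potential harm" and, on that ground, provides for no data monitoring committee, interim analysis or stopping rules. The Participant eligibility section excludes people allergic to the tape.

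Pain and knee function are primary outcomes. Under Primary outcome, "VAS was used to evaluate the pain of PFPS patients before and after intervention", and the Data collection section schedules the primary and secondary outcomes "at baseline, at 4 weeks of intervention, and at 6 weeks of intervention".

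**The concern.** Expectedness is normally a property noted about an adverse event once it is on record. Here it decides whether the event is reported in the first place. The article does foresee at least one kind of harm, since tape allergy is an exclusion. It also has staff ask about pain after each taping and compare pain during a half-squat. A member of staff could reasonably regard mild skin irritation, or some soreness after lunges and kicks, as expected and therefore outside the rule. Another could report the same event.

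With no monitoring committee or stopping rule, event reporting is the only safety check that the article describes. If that check can pass over foreseeable events, the number of events eventually reported may be too low, and it may depend on who applied the word and how.

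**Working it through.** This is a question of wording. The article states no adverse event rate, safety endpoint or safety power, so there is no planned figure to reproduce. The check compares the texts and then gives a sense of scale.

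**Step 1. The texts side by side**

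| Place | What it covers | Limited to unexpected events? |
|---|---|---|
| Safety measurements, first sentence | Reporting to the research assistant; causality assessment | Yes, by its wording |
| Safety measurements, second sentence | Escalation to project leader and ethics committee | No |
| Monitoring | Expects no harm | Implies that any harm could count as unexpected |
| Participant eligibility | Excludes tape allergy | Shows that tape reactions are foreseen |

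Two readings follow.

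- *Broad:* nothing is expected, so every harm is unexpected and all are reported.
- *Narrow:* a foreseeable, non-severe event is not unexpected, so it need not be reported or assessed.

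The second sentence does not settle the matter. Grammatically, *severe* may apply to the injury alone or to both kinds of event. The research assistant also has to learn of an event before escalating it, and the only stated route to the assistant is the first sentence.

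**Step 2. What else would catch such an event**

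- Skin irritation: none of the primary or secondary outcomes (VAS, Lysholm, the two balance tests, isokinetic strength, joint position sense) measures it.
- Knee pain: VAS, together with the pain and swelling items of Lysholm, records the state of the knee at weeks 4 and 6 in every arm. A flare that arises and settles between those visits could be missed.

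**Step 3. Scale, under assumed rates**

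Inputs: the Sample size calculation section gives 72 participants, about 18 per group. Tape, real or placebo, is used in three groups: 3 × 18 = 54. Real tape is used in two: 2 × 18 = 36. The reaction rate p is not in the documents and is assumed to be 2%, 5% or 10%.

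Formulas: expected cases = n × p; chance of at least one case = 1 − (1 − p)^n.

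| p | n = 54 (all taped) | n = 36 (real tape only) |
|---|---|---|
| 2% | 54 × 0.02 = 1.1; 1 − 0.98^54 = 66% | 36 × 0.02 = 0.7; 1 − 0.98^36 = 52% |
| 5% | 54 × 0.05 = 2.7; 1 − 0.95^54 = 94% | 36 × 0.05 = 1.8; 1 − 0.95^36 = 84% |
| 10% | 54 × 0.10 = 5.4; 1 − 0.90^54 = 99.7% | 36 × 0.10 = 3.6; 1 − 0.90^36 = 98% |

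The second column is there because the placebo tape carries 0% tension and may not irritate at the same rate. On the broad reading every case is recorded. On the narrow reading the non-severe ones need not be.

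**The case against.** The best reply is that the rule may exclude nothing. The text never says that *only* unexpected events are reported, the next sentence takes in other adverse events without that limit, and a protocol that expects no harm makes any harm unexpected. That stands as far as it goes. It means that events *could* be lost, not that they will be. It does not remove the ambiguity, because the eligibility criteria show that tape reactions are foreseen.

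A second reply is that elicitation methods and adverse event forms belong to the full protocol, which is not shown. This is also right, and their absence from the article is not held against it. The point rests on a criterion that the article does state.

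Several stronger conclusions are tempting, but the documents do not support them.

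- *Knee pain would go uncounted.* VAS and Lysholm record it at scheduled visits in all four groups. Only a transient flare is at risk.
- *The safety result is biased towards none.* No safety endpoint or between-group safety comparison is defined, and severe injuries are still escalated.
- *Control participants are seen only at assessments, so counts are not comparable by arm.* The Abstract says that all four groups received sessions three times a week, while the CON section describes usual activity. Contact in that arm is contradictory, so the inference has no firm base.
- *No events among the 36 Tan Tui participants would rule out only rates above 8%, so omissions matter.* The bound is correct, 1 − 0.05^(1/36) = 0.080, but it follows from the number 36 alone and would hold with perfect recording.

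**Conclusion.** The concern holds in a limited form. The reporting criterion is badly fixed: two adjacent sentences and the Monitoring section do not agree on which adverse events are captured. On the literal reading, non-severe foreseeable events could escape both reporting and causality assessment, and adverse events could be under-counted.

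The size is small in absolute terms. Under the assumed 2% to 10% rates it is at most about 1 to 5 tape reactions among 54 participants, less any that are severe, and it is zero if staff adopt the broad reading. In a trial of this size, the loss of a few events could still make the difference between reporting some tape reactions and reporting none. The efficacy analysis is untouched.

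The conclusion rests on the wording as published and on rates that the documents do not supply. A full protocol that already requires all adverse events to be recorded would resolve it.

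**What to change.** In the Safety measurements section, replace the opening words *Any unexpected adverse events* with *All adverse events, expected or unexpected, in all four groups*. Then:

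- note expectedness as an attribute of each recorded event, not as a condition for recording it;
- reconcile the escalation sentence with this, making clear whether *severe* qualifies the sports injury alone or every event named there (which events warrant escalation or withdrawal is for the sponsor to decide);
- record events in the same way in every arm at the existing week 4 and week 6 visits, covering the time since the previous visit;
- report counts by randomised group.

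The cost is a few extra lines on the case report form. No visit is added, and sample size, alpha and power stay as they are.

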### Study design

This is a single-blind randomized controlled trial that recruited 72 eligible early PFPS patients and randomly divided them into 4 groups: TT + KT group, TT + KTp group, KT group, and CON group with a ratio of 1:1. The TT + KT group was intervened with TT combined with intramuscular tape; the TT + KTp group was intervened with TT and intramuscular tape with placebo technical intervention; the KT group was intervened with intramuscular tape alone; the CON group was performed with routine activities. Measurements will be taken at baseline, mid-intervention (4 weeks), and post-intervention (6 weeks) to examine the maintenance of any intervention effects.

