#### Placebo kinesio taping

The application of the patch was the same as before, but the tension of the patch was 0%, and the patch was only attached to the ankle joint of the subject without any stretching. Both functional correction taping and placebo taping techniques were applied to the subject’s bilateral quadriceps and taped once every 5 days [39, 40].

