### Statistical analysis

Statistical analysis will be performed by the Statistical Package for Social Sciences (The Statistical Package for Social Sciences, SPSS 23, SPSS Inc., Chicago, IL, USA). ShaPiro Wilk will be used to test whether the variables of the two-way multivariate analysis of variance conform to the normal distribution. One-way multivariate analysis of variance will be used to compare the baseline age, height, and weight data of participants, to explore whether there is homogeneity between groups. Descriptive statistical analysis will be conducted in the form of mean ± standard deviation. Two-way multivariate analysis of variance will be used to perform inference analysis on the effect of the intervention group (e.g., TT + KT, KTp + TT, KT, CON) and time (e.g., pre-intervention, during intervention, post-intervention), in order to examine group effect and time effect and The interaction effect of time and group. Pairwise comparisons of variables with significant effects in ANOVA will be conducted by post hoc analysis and Bonferroni correction to find time effects by group and group effects by time. According to Cohen’s method, the effect size will be divided into large (0.8), medium (0.50–0.79), and small (0.20–0.49) to judge the significance of the intervention effect [55]. *P* < 0.05 means there is a significant difference, and *P* < 0.01 means the difference is extremely significant.

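### Routine adverse-event reporting is tied to the 6-week intervention period, which leaves out baseline-test injuries and late tape or Tan Tui reactions and leaves the week-6 tests unclear

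*Protocol article*

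**What the plan says.** The Safety measurements section of the protocol article has two reporting sentences. The routine one covers unexpected adverse events "that occurred during the 6-week intervention period will be reported to the research assistant". It adds that the causal link to Tan Tui and to taping will be assessed. The second is an escalation rule: "If a severe sports injury or other adverse event occurs, the research assistant will immediately report to the project leader". It also names the ethics committee, and its stated result is a decision on whether the participant should withdraw. This second sentence has no time limit.

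On test visits, the Study design section says "Measurements will be taken at baseline, mid-intervention (4 weeks), and post-intervention (6 weeks"). The Statistical analysis section labels the time levels "pre-intervention, during intervention, post-intervention". The Data collection section instead dates the last two assessments by weeks of intervention, four and six. No visit after week 6 is described. The one later communication mentioned is release of the participation reward: "It will be released via WeChat after 6 weeks of intervention".

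On exposure, real and placebo tape are both "taped once every 5 days". The Tan Tui section raises the static hold from 1 to 5 seconds over the last five weeks. The control group only continues its usual activity. Under Monitoring, the trial has no monitoring committee, no interim look and no stopping rule.

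**The concern.** The routine window is narrower than the period in which study procedures can cause harm.

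- **Before the window.** The baseline visit includes isokinetic testing ("Knee flexion and extension tests were performed 5 times each"), eyes-closed single-leg stance and single-leg reaching, in patients selected for a painful knee. An injury there comes before the intervention period.
- **At its edge.** Staff cannot tell from the text whether an injury at the week-6 tests is reportable.
- **After it.** A skin reaction to the last tape, or a knee flare after the last and longest-held Tan Tui sessions, may appear once routine reporting has closed and no further visit is described.

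With no monitoring committee, Safety measurements is the only dedicated safety procedure in the article. A later statement that the treatment was well tolerated would rest on a record that closes too early to show late reactions.

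**Working it through.** The plan gives no figure on this point to reproduce. The check compares the window with the visits and counts taping days.

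**1. Test visits against the window.** Inputs: 72 patients (Sample size calculation) and three assessments (Study design). Each visit is 72 × 1 = 72 patient sessions.

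| Visit | Sessions | Position |
|---|---|---|
| Baseline | 72 | Before the window |
| Week 4 | 72 | Inside |
| Week 6 | 72 | At the edge: post-intervention in Study design and Statistical analysis; six weeks of intervention in Data collection |

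Only the 72 baseline sessions are clearly outside.

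**2. Last tape against the window.** Inputs: one taping every 5 days (Placebo kinesio taping section, covering both tape types) and a period of 6 × 7 = 42 days. Assumptions, because the article does not state them: first taping on day s, no new tape on day 42 itself, and each tape worn until the next change would be due. With L the last application day before day 42, days past the window = (L + 5) − 42.

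| s | L | Tape due off | Days past day 42 |
|---|---|---|---|
| 0 | 40 | 45 | 3 |
| 1 | 41 | 46 | 4 |
| 2 | 37 | 42 | 0 |
| 3 | 38 | 43 | 1 |
| 4 | 39 | 44 | 2 |

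The range is 0 to 4 days. Counting the application day as the first of five wear days lowers each non-zero entry by one (for s = 1, worn through day 45, 3 days past). Earlier removal shortens it further. Patients potentially affected: three taped arms × 18 = 54.

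**3. Late exercise reactions.** Two Tan Tui arms × 18 = 36 patients reach the longest hold at the end of the six weeks. The article gives no rate of delayed flares, so no count can be derived.

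**4. Which arms lose what.** All four arms have the same test visits, so unreported test injuries are lost alike. Reactions caused by tape or Tan Tui and starting after week 6 can occur only in the three arms that receive one or both. Late knee complaints unrelated to study treatment are lost in every arm, including control.

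**The case against.** The strongest reply is that the routine sentence does not stand alone. The escalation rule has no time limit, so a severe injury at baseline or after week 6 is not excluded. That stands, and it rules out the reading that events count only if they fall within the six weeks. The rule is not a full remedy. It works through the research assistant and leads to a decision about withdrawal, which has little use once the intervention is over, and no later contact is described through which an event would come to light. If its second limb is read as covering any adverse event, the two sentences disagree on whether a window applies.

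A reader might also infer that the final tests are plainly outside the window, or that losing test injuries favours the active arms. The documents support neither. Data collection dates the last visit by weeks of intervention, and the tests are common to all arms.

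Nor does a test injury lack a possible causal classification. The article defines no categories, so a finding of unrelated to tape or Tan Tui remains available.

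Three further replies have some force. Pain and Lysholm scores at week 6 would show a knee flare present by then, but not one that starts later, and they do not record skin reactions. Tape allergy is an exclusion, which lowers the risk without removing it. Finally, an article leaves operational safety detail to the full protocol. That excuses what is missing, but here the window is stated, and stated too narrowly.

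**Conclusion.** The point holds in limited form. As written, routine reporting omits injuries at 72 baseline sessions and any tape or Tan Tui reaction starting after week 6, and it leaves 72 week-6 sessions ambiguous. The last tape may outlast the window by 0 to 4 days in up to 54 patients, on the assumptions about start day and wear time above; zero is within the range. Because severe events have their own rule without a time limit, the gap mainly concerns less serious events.

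A reader might infer a general bias in the harms record towards the active arms. The documents support this only for late treatment-caused reactions. Their size is unknown, and no between-arm comparison of harms is planned. The primary outcomes and their analysis are not affected. The correction is worth making because the rule is explicit, cheap to change and the only safety procedure the article describes.

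**What to change.** In Safety measurements, replace the 6-week window with one that runs from the first study procedure to a short fixed interval after the latest of the last session, tape removal and final test, identical in all four arms. Seven days is an example, not a figure from the documents. State that events at all three test visits are included. Put the same adverse-event question to every patient at the final visit and in one closing message. WeChat could carry it, since the reward is released that way, but that release is a payment and not yet a follow-up contact. Naming study test procedures as a possible cause is optional.

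The cost is a one-sentence change to the window, a line for the question, 72 messages and a few more minor events recorded.
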